### Outcomes

The evaluation of the HAPPY Study will be done using three different quantitative instruments to report on the physical activity levels, students’ behaviour in class, and sources of social support to be physically active. Measurement of these three data sets, will allow the research team to analyse the effects of each component of the intervention; how playground markings can effect physical activity levels during lunch and recess; how this increase, as well as social skills taught through the Peaceful Playgrounds intervention may impact students behaviour during class; and how teacher and student development influences from where, and how frequently students’ receive encouragement to by physically active.

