## Methods/Design

### Study Design

The Healthy Active Peaceful Playgrounds for Youth (HAPPY) study is a 12 month, primary school-based intervention and will be evaluated using a cluster controlled trial with a stepped wedge design. Ethics approval has been obtained from an Australian University Human Ethics Committee (HREA5201500676) as well as from the New South Wales Department of Education and Communities (SERAP2015423). The HAPPY Study is registered with the Australian and New Zealand Clinical Trials Registry (ACTRN12616000575437). Principals, teachers and parents will provide written informed consent.

Following the recruitment process, data will be collected on students’ physical activity levels during lunch and recess, students’ on-task behaviour during class following lunch, and from whom the students receive social support from to be physically active. The intervention will be rolled out in a stepped wedge design. This means that all schools will start as ‘control’ schools and that the intervention will staggered across the 12-month period of the study (three steps in total) with data will being regularly collected across the period (Fig. 1). The stepped wedge design allows for an analysis of the interventions effectiveness and efficacy. As well as having the added benefit of ensuring all schools receive the intervention [16] (i.e., playground markings and teacher training). This benefit is often absent in classic Randomised Control Trials, where control groups may receive no immediate benefit from participating in research studies. This was the main rationale behind adopting this stepped wedge design.

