### Intervention design

The Peaceful Playgrounds Program is a primary school-based package that uses permanent playground markings, teacher training and accompanying resources to promote physical activity in playgrounds, teach fundamental movement skills, and support social skill development in students. The Peaceful Playgrounds Program will be used in the HAPPY Study as the intervention, and the effects of this on both physical activity levels, and behaviour in students measured.

Several research studies using either the Peaceful Playgrounds Program, or a similar playground based intervention, have shown changing playgrounds in primary schools to be more conducive to play, and supporting school teachers and students to make use of these spaces can significantly increase levels of physical activity, enjoyment of physical activity and improved social interaction skills (i.e. conflict resolution, and sharing) [17–19]. Peaceful Playgrounds will run a multi-component intervention that incorporates elements of environmental, and social intervention, as well as a teacher professional development to increase physical activity participation.

The environmental component of intervention involves the instillation of multi-coloured playground markings that act as visual prompts for students and teachers to be physically active. The markings will be designed specifically for each participating school, and teaching resources will be provided including games, activity suggestions and units of work that can be performed in relation to the markings. Accompanying equipment and play resources will be provided to schools to support engagement with the playground markings and increase physical activity.

Professional learning support will be offered to teachers at participating schools, which will include strategies for initiating play during breaks, games and activities that support the development of social skills in students such as sharing and self-regulation, and methods of supporting conflict resolution for the playground. The teacher training will also include an online network to provide a platform for teacher self-reflection, discussion forums and opportunities to interact with other participating teachers and the research team.

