A Student Ambassador program will be implemented during the intervention to increase the social support students receive to be physically active. Selected students from Stage 3 (years 5 and 6) classes at each school will undertake a student leadership program to develop knowledge and skills to become physical activity ambassadors during break times. The students will be taught techniques from the Peaceful Playgrounds Program to initiate games and encourage social inclusion in their peers.

The Peaceful Playgrounds intervention is expected to increase vigorous physical activity levels in children, encourage participation and enjoyment of physical activity, and structure play in a way that supports socialisation and emotional well-being in children. The HAPPY Study will determine if Peaceful Playgrounds is an effective, efficacious, and scalable intervention.

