### Physical activity during recess and lunch

Observational data will be collected on student’s physical activity levels during lunch and recess breaks, and their utilisation of playground spaces for physical activity recorded using the System for Observing Play and Recreation in Communities (SOPARC) tool (CIAFEL, Portugal: http://activelivingresearch.org/soparc-system-observing-play-and-recreation-communities). This tool will collect student’s sex, their level of physical activity and environmental factors (i.e. time of day, temperature, recess/lunch break, presence of supervision).

SOPARC is a sampling technique in which systematic and periodic scans of individuals and environmental factors within predetermined target areas are made. Each school will have two predetermined target areas, identified by the Principal of participating schools as areas that students use frequently during recess and lunch. Following SOPARC protocols developed in a previous study [20, 21], trained researchers will complete two scans of each areas at both recess and lunch, three times during each term the study is running. The researchers are blind to the conditions of the intervention. Each school in the study will therefore be scanned 12 times each term, for a total of 288 scans across all schools during the study.

A scan involves panning from left to right, and coding each student in the area by sex (male or female), intensity of activity (Sedentary, Walking or Vigorous), and whether they are a Child, Teen, Adult or Senior. Additional data recorded for each scan will include; 1. Weather variables including temperature, rain and UV levels; 2. Time of day the observations were collected, and whether this was a lunch or recess period; 3. What type of activity the students are engaged in (i.e. handball, football, dancing, clapping games) and; 4. Teacher supervision and direction of physical activity. The SOPARC tool has been used by this research team to collect physical activity and sun-safe behaviours in primary schools, and was found to be efficient to use and had high degree of reliably, with an Intraclass Corelation Coefficient (ICC) of .912 [21].

Analysis of data collected with SOPARC will be done at an individual school level, between all schools during the same collection period and then completed on all data collected during the study.

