### Social Support

The Physical Activity Social Support Scale [25] will be given to all students in Stage 3 (years 5 and 6) classes as a survey, and used to collect self-report data measuring sources of adult and peer support of physical activity. Test-retest reliability of the scale is strong (ICC = .88) and the Internal consistency of the items was evaluated at α = .77 [26]. The tool is a 15 min survey with nine questions about how often students receive encouragement to be physically active and from who. The response to each question is divided into adult male, adult female and other children (peers), and anchored to a six-point Likert scale (None = 0, Often = 1, Sometimes =2, Almost Daily = 3, Daily =4,Don’t know = 6). This tool will be used to measure the effects of the teacher training, and student ambassador components of the Peaceful Playgrounds intervention.

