A key strength of this study is the stepped wedge cluster controlled trial design. The design of the study means that time can be used as a variable to measure the effect of the intervention overtime. The design of the study also enables the research team to run the intervention in all schools over the 12-month study period. While this is thought to be ethical [30], it is also likely to decrease attrition.

If this study is successful in increasing students’ physical activity levels and modifying students’ behaviour, future research could include examining which aspects of the intervention produce which effects.

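### The protocol claims component-level effects and observers blind to condition, but it describes one package staggered by school and playground scans made in plain view of that package

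*Protocol article*

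**What the plan says.** **Components.** The Outcomes section states "Measurement of these three data sets, will allow the research team to analyse the effects of each component of the intervention". It then pairs markings with activity at breaks, activity and social skills with classroom behaviour, and teacher and student development with encouragement to be active. The Social Support section says of the survey: "This tool will be used to measure the effects of the teacher training, and student ambassador components of the Peaceful Playgrounds intervention". The opening of the Discussion again asks about markings, and about training and student leadership, separately.

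**Structure of the intervention.** Under Intervention design, "Peaceful Playgrounds will run a multi-component intervention that incorporates elements of environmental, and social intervention, as well as a teacher professional development". On the ambassadors: "A Student Ambassador program will be implemented during the intervention to increase the social support students receive to be physically active". Study Design has every school begin as control and receive the intervention in one of three steps. The recruitment section randomises schools to step groups; it does not randomise components. The Discussion closes by saying that, if the study succeeds, "future research could include examining which aspects of the intervention produce which effects".

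**Blinding.** The section on physical activity during recess and lunch says of those doing the SOPARC scans: "The researchers are blind to the conditions of the intervention". The same section has them pan across a playground area by eye, code each student's intensity, and record activity type and teacher direction. The markings are described under Intervention design as "multi-coloured playground markings that act as visual prompts for students and teachers to be physically active".

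**The concern.** Both statements give the trial a property that the described design does not have.

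The first would let a change on one instrument be reported as the effect of one component, for example a SOPARC change credited to the markings. Every outcome is exposed to the whole package, so measuring with a different instrument does not isolate a component. The Outcomes and Discussion sections also disagree on whether this trial or a later one addresses the question.

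The second would let human coding of sedentary, walking or vigorous activity be presented as assessor-blinded. If observers can tell whether the program is in place, expectation can shift the coding, and a reader relying on the blinding sentence would discount that risk.

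**Working it through.** There is no stated figure to reproduce. The first part is a question of identifiability, the second a comparison of sections.

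**1. Can component effects be separated?**

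Inputs from the article: six schools, three steps, all schools starting as control, one intervention with environmental, teacher and student-leadership elements.

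Assumptions, not stated in the article: two schools per step; four periods (a baseline term, then one step per term); all components starting together at a school's step. The four terms agree with the article's own scan figures: 288 / (6 × 12) = 4.

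Design matrix: intercept, 5 school indicators, 3 period indicators, then 0/1 exposure indicators.

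- One package indicator: 1 + 5 + 3 + 1 = 10 columns, rank 10. The package effect is estimable.
- Three component indicators with a common start: 1 + 5 + 3 + 3 = 12 columns, rank 10. The three indicators are the same column, so two component contrasts are lost.
- The same without period effects: 1 + 5 + 3 = 9 columns, rank 7. The deficit is again two.
- Component starts spaced one period apart within each school: 12 columns, rank 12. Separation would then be possible, but the article describes no such spacing.

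**2. Do separate instruments rescue the claim?**

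The article's own text crosses the pathways. Teacher training covers ways to get play going at breaks, ambassadors are taught to start games, and equipment is supplied in order to raise activity. All three act on what SOPARC measures, as the markings do. A SOPARC change therefore belongs to the package.

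**3. Can the playground observers be blind?**

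| What the observer does | What is there after roll-out |
|---|---|
| Scans the playground by eye | Permanent coloured markings intended to be noticed |
| Records the type of activity | Games tied to the markings, new equipment, ambassador-led play |
| Records teacher direction of activity | Teachers trained to initiate play |

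The task itself requires attention to features that the intervention introduces.

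**4. How much of the data is affected?**

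Total school-terms: 6 × 4 = 24. Schools starting at the first, second and third step contribute 3, 2 and 1 intervention terms.

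- Two schools per step: 2×3 + 2×2 + 2×1 = 12 of 24.
- Most early starters, with at least one school per step (4, 1, 1): 4×3 + 1×2 + 1×1 = 15.
- Most late starters (1, 1, 4): 1×3 + 1×2 + 4×1 = 9.

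The range is 9 to 15 of 24.

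**The case against.** **A common start is not stated.** The article gives no component dates, and the figure showing the design is not available here. A reader might infer that the documents prove a simultaneous start and that no component contrast could ever be estimated. They do not: spaced starts would restore full rank. What stands is that no separation is described. The conflict between the Outcomes and Discussion sections does not depend on start dates.

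**The data carry some information on pathways.** The survey separates adult from peer sources of support, and each scan records activity type and teacher direction. This is a fair point, and it makes component attribution exploratory rather than empty. It is still observational and does not support the flat statement that component effects will be analysed.

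**The analysis already targets the package.** The Statistical methods section relates the intervention as a whole to each outcome and describes no component term, and the Discussion supplies a caveat. This limits the harm to interpretation. The claims in Outcomes and Social Support remain as written.

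**Blindness may mean something narrower.** It is undefined and could mean that observers are not told the schedule or allocation. Baseline scans also precede randomisation, and the markings are not expressly placed inside the two target areas. A reader might infer that the blinding statement is false in every sense and at every visit; the article does not support that. But the sentence is unqualified and refers to condition. Even if the markings lay outside a target area, equipment and organised games could reveal the condition. The reported SOPARC reliability (ICC .912) concerns agreement, not bias from knowing the condition.

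**Conclusion.** Both points hold as errors in what the article claims.

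The component claim conflicts with the article's own Discussion and with the design it describes. Assuming components start together at each school's step, only the package effect is estimable on each outcome, with two component contrasts lost among three components. Without that assumption, the article still describes no arm or period that separates them.

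Blinding of SOPARC observers to condition is not credible once the program is in place. That covers about 12 of 24 school-terms under the assumed equal steps, and 9 to 15 otherwise; the conclusion does not change across that range.

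A reader might go further and infer that the trial cannot evaluate the program at all. This point does not support that: the package effect remains estimable, and what is affected is how the results may be attributed and how the activity measure may be described.

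**What to change.** - **Outcomes and Social Support:** state that each outcome estimates the effect of the whole package, and label any attribution to a single component as exploratory, in line with the Discussion. The component questions at the start of the Discussion should be read the same way.
- **Physical activity during recess and lunch:** replace the blinding sentence with what observers are actually kept unaware of (for example, the step schedule, if that is so). Do not describe SOPARC as assessor-blinded to condition, and name observer bias as a limitation.

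The cost is wording only. Sample size, schedule and data collection are unchanged. The claims become slightly less favourable.

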### Physical activity during recess and lunch

Observational data will be collected on student’s physical activity levels during lunch and recess breaks, and their utilisation of playground spaces for physical activity recorded using the System for Observing Play and Recreation in Communities (SOPARC) tool (CIAFEL, Portugal: http://activelivingresearch.org/soparc-system-observing-play-and-recreation-communities). This tool will collect student’s sex, their level of physical activity and environmental factors (i.e. time of day, temperature, recess/lunch break, presence of supervision).

SOPARC is a sampling technique in which systematic and periodic scans of individuals and environmental factors within predetermined target areas are made. Each school will have two predetermined target areas, identified by the Principal of participating schools as areas that students use frequently during recess and lunch. Following SOPARC protocols developed in a previous study [20, 21], trained researchers will complete two scans of each areas at both recess and lunch, three times during each term the study is running. The researchers are blind to the conditions of the intervention. Each school in the study will therefore be scanned 12 times each term, for a total of 288 scans across all schools during the study.

A scan involves panning from left to right, and coding each student in the area by sex (male or female), intensity of activity (Sedentary, Walking or Vigorous), and whether they are a Child, Teen, Adult or Senior. Additional data recorded for each scan will include; 1. Weather variables including temperature, rain and UV levels; 2. Time of day the observations were collected, and whether this was a lunch or recess period; 3. What type of activity the students are engaged in (i.e. handball, football, dancing, clapping games) and; 4. Teacher supervision and direction of physical activity. The SOPARC tool has been used by this research team to collect physical activity and sun-safe behaviours in primary schools, and was found to be efficient to use and had high degree of reliably, with an Intraclass Corelation Coefficient (ICC) of .912 [21].

Analysis of data collected with SOPARC will be done at an individual school level, between all schools during the same collection period and then completed on all data collected during the study.

### Behaviour

Student’s on-task behaviour during class time will be measured using the Behavioral Observation of Students in Schools (BOSS) app [22]. Interobserver agreement for the BOSS tool have been consistently reported as high, with kappas ranging from .93 to .98 [23, 24].

Trained researchers will be observing Stage 3 (years 5 and 6) classes following lunch breaks to record the behaviour of students using the BOSS app. Five students will be identified by each participating school, and these students’ (*n* = 30) behaviour will be recorded at each data collection point of the study.

Student behaviour is recorded directly into an iPad using the BOSS app [22], which first codes a target student as engaged (Momentary), or non-engaged (Partial). If a student is identified as being engaged, they are then coded as being either 1. Actively Engaged (i.e. writing, reading aloud, raising a hand, talking to a teacher about the material); 2. Passively Engaged (i.e. listening to a lecture, looking at an academic worksheet, silently reading assigned material). The coding for non-engaged students includes 1. Off-Task Motor (i.e. students being out of their seat, aimlessly flipping pages or worksheets, drawing or writing not related to academic material); 2. Off-Task verbal (i.e. talking to another student about non-academic material, making sounds such as humming, calling out answers or comments to teachers) and; 3. Off-Task Passive (i.e. staring out the window, listening to other students talk about non-academic material, looking around the room).

### Social Support

The Physical Activity Social Support Scale [25] will be given to all students in Stage 3 (years 5 and 6) classes as a survey, and used to collect self-report data measuring sources of adult and peer support of physical activity. Test-retest reliability of the scale is strong (ICC = .88) and the Internal consistency of the items was evaluated at α = .77 [26]. The tool is a 15 min survey with nine questions about how often students receive encouragement to be physically active and from who. The response to each question is divided into adult male, adult female and other children (peers), and anchored to a six-point Likert scale (None = 0, Often = 1, Sometimes =2, Almost Daily = 3, Daily =4,Don’t know = 6). This tool will be used to measure the effects of the teacher training, and student ambassador components of the Peaceful Playgrounds intervention.

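### The social-support survey does not identify teachers or ambassadors as sources, so it can show the whole package's effect on adult and peer encouragement but not the component effects assigned to it

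*Protocol article*

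**What the plan says.** All places are in the protocol article.

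- **Social Support** describes the instrument as "used to collect self-report data measuring sources of adult and peer support of physical activity". It has "nine questions about how often students receive encouragement to be physically active and from who". On the recorded source it says: "The response to each question is divided into adult male, adult female and other children (peers". Frequency is then rated on a six-option scale.
- **Social Support**, last sentence, gives the use: "This tool will be used to measure the effects of the teacher training, and student ambassador components of the Peaceful Playgrounds intervention".
- **Outcomes** says that the three instruments together "will allow the research team to analyse the effects of each component of the intervention". The survey's share of that task is to show "how teacher and student development influences from where, and how frequently students’ receive encouragement to by physically active".
- **Intervention design** presents markings, teacher development and the ambassador scheme as parts of one multi-component programme. On the ambassadors it says: "Selected students from Stage 3 (years 5 and 6) classes at each school will undertake a student leadership program". The survey goes to all pupils of that same stage.
- **Discussion** leaves to later studies the question of which part of the intervention causes which effect.

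**The concern.** The survey is assigned two component-specific questions: what teacher training does, and what the ambassadors do. Both depend on knowing that the encouragement came from a teacher or from an ambassador. The recorded categories give the sex of an adult, or the fact that the source was another child. They give neither role nor setting.

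Two things are at stake. First, interpretation: a rise in the adult-female column could be reported as a result of teacher training when the data show only that women encouraged pupils more often. Second, sensitivity: encouragement from home and from friends enters the same columns and is not the target of the intervention, so a real change at school shows up as a smaller change in the recorded score.

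**Working it through.** The plan gives no sample size, power or effect size for this outcome (the Sample size calculation section concerns physical activity observations), so there is no figure to reproduce. The check compares what is recorded with what is to be concluded.

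**Step 1: which source falls in which column, as described**

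| Source of encouragement | Column | Others in the same column |
|---|---|---|
| Female teacher | adult female | mother, other female relative, female coach |
| Male teacher | adult male | father, other male relative, male coach |
| Student ambassador | other children (peers) | friends, classmates, siblings |

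No column belongs to teachers or to ambassadors alone. Ambassadors are Stage 3 pupils and the respondents are Stage 3 pupils, so ambassadors are ordinary peers as far as the form is concerned.

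**Step 2: what can be estimated**

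- *Effect of the whole intervention on adult-male, adult-female and peer encouragement:* yes. The article describes a randomised roll-out order (Sample size calculation; Recruitment and study participation) and a comparison of control with intervention periods (Statistical methods).
- *Change in encouragement specifically from teachers or from ambassadors:* no, from the columns as described.
- *Separate effect of the teacher-training or ambassador component:* no, for two independent reasons. The source is not identified, and no step or arm is described in which a single component is delivered. Solving either problem would leave the other.

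**Step 3: how much dilution could matter (illustration only)**

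Let s be the share of adult encouragement that comes from teachers. The documents do not give s. Assume that sources add up within a column, and compare the adult score with a teacher-only score of the same mean and SD. A proportional change c in teacher encouragement then appears as s × c in the adult score. Required sample size varies as 1/effect², so it is multiplied by 1/s²:

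- s = 0.75: 1/0.5625 = about 1.8
- s = 0.50: 1/0.25 = 4
- s = 0.25: 1/0.0625 = 16

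The width of this range shows that the size is not known. It does not estimate the loss in this trial.

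**The case against.** **The package effect is still estimable.** This stands. Encouragement from parents and friends is present in both control and intervention periods. It weakens the contrast but does not by itself bias it, provided the comparison uses the staggered, randomised order.

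**The adult/peer split is a rough proxy**, with adults standing for teacher training and peers for ambassadors. This stands in part. The split can show whether a change is on the adult or the peer side, but it cannot separate school from home, which the teacher-training claim needs.

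**The nine questions are not shown.** This also stands. An item that names the school setting cannot be excluded, and a condensed article need not print the instrument. However, the article does state both the source categories and the intended use, and these two statements do not match.

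**Teacher behaviour is observed elsewhere.** The playground scans record teacher supervision and direction of activity. That is useful evidence on what teachers do, but it is not pupil-reported encouragement and does not rescue the survey's assigned task.

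A reader might go further and infer any of three things that the documents do not support:

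- *That nothing stated about social support can be derived.* The effect of the whole package on adult and peer encouragement can be.
- *That changes at home would be credited to teacher training.* For that, home changes would have to follow the staggered steps, and the article gives no reason to expect this.
- *That pupils already encouraged daily by a parent remove a definite fraction of the effect.* No baseline distribution is given. With nine questions, a pupil at the top on one can still move on others. How pupils combine several adults in one answer is not described.

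**Conclusion.** The point holds in a limited form. As described, the survey supports a conclusion about the effect of the whole intervention on overall adult and peer encouragement, diluted by sources outside school. It does not support the teacher-specific and ambassador-specific conclusions that Outcomes and Social Support assign to it. Bundled delivery rules out component attribution independently, and the Discussion already treats that question as future work, so the article is also inconsistent with itself.

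This is mainly an overstated claim. It does not make the outcome unusable. The loss of sensitivity cannot be quantified from the documents. The conclusion assumes that the three columns are the only record of source and that no item names a role or the school setting. Since the items are not printed, confidence is medium.

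**What to change.** **Main change.** Reword Outcomes and Social Support so that the survey outcome is the effect of the whole intervention on encouragement from adults and from peers. For example: *The survey will estimate the effect of the intervention as a whole on how often pupils report encouragement from adults and from other children. It will not be used to draw conclusions about teacher training or the ambassador programme separately.* The component questions listed in the Discussion should be brought into line. This costs nothing and removes the conflict with the statement there about future research.

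**Optional addition.** If encouragement from teachers or ambassadors is to be reported, keep the present columns for comparability and add two source columns, one for a teacher at the pupil's school and one for a student ambassador or leader at the pupil's school. A column for any student at the school would not be enough, because it would still pool ambassadors with classmates and school friends. The columns must be in place from baseline, since a source not recorded then cannot be recovered later.

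The cost is a longer form. Three columns by nine questions is 27 responses and five columns is 45, which is 18/27 = 67% more. If time scales with responses, the 15-minute survey takes about 15 × 45/27 = 25 minutes. The published reliability figures (ICC .88, α .77) would not cover the new columns. Even with them, the result would be a package effect on teacher-sourced or ambassador-sourced encouragement, because the components are still delivered together.
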